## Background

Emergency Department (ED) crowding (and access block) has been described as the most serious issue currently confronting EDs [1-3]. The demand for ED services exceeds any growth that can be explained by population increase [4]. A recent Australian Institute of Health and Welfare (AIHW) report identified that “between 2009–10 and 2010–11, ED presentations increased in all states and territories, with increases ranging from 1.6% in Tasmania to 8.1% in Western Australia” [5], p vii. ED crowding has been linked to a range of adverse outcomes for patients and staff, including increased medical errors, increased patient mortality, patient dissatisfaction, high levels of work-related stress, decreased morale among ED staff and decreased capacity of EDs to respond to mass casualty incidents [2,3,6,7].

Ambulance usage is also increasing annually. In Western Australia (WA), St John Ambulance Western Australia (SJA-WA) activity in the Perth metropolitan area increased by 23% to 171,462 cases attended in the 2010/11 financial year from138,996 cases in 2006/07 [8]. For the year 2012, SJA-WA paramedic crews in metropolitan Perth attended a total of 132,862 cases and 105,327 (79.3%) were transported to ED. (“unpublished data” provided to [name] by SJA-WA.) Increasing numbers of ambulance arrivals are one of the key drivers of ED demand and also increased episodes of ramping [9]. There is growing recognition that not all patients attended by paramedics actually need to be transported to ED. As part of a major overhaul of emergency services in the UK [10], the concept of ‘emergency care practitioners’ (EmCPs) emerged as an alternative model of ambulance paramedic response [10-12]. Initial reports showed that EmCPs were dealing with “54% of patients without the need for an immediate referral to another healthcare professional or emergency transportation to ED” [11]. A cluster randomised trial in the UK reported reduced ED attendance associated with Paramedic Practitioner (a similar role to EmCP) attendance, whilst maintaining patient satisfaction and safety [13].

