### Phase 1: Collect baseline data

Over a 3 month period, we will include all patients within the Perth metropolitan area attended by SJA-WA paramedics and transported to one of the11 Perth EDs. The paramedics will routinely indicate on the e-PCR whether, in their opinion, they consider that the patient they attended could have *potentially* been managed by an ‘extended care paramedic’ through either a) ‘see and treat’ , or b) ‘see and refer’ strategies. (All paramedics will be emailed a clinical circular outlining the process for indicating on the e-PCR the possible alternative pathways.) In addition, the details of any patients attended by SJA-WA paramedics but not transported to ED (currently recorded as ‘Ambulance Not Required’ - ANR) will also be captured as part of the study.

The ED disposition and other clinical outcomes of the patients in this study cohort will be obtained via the WA EDIS data, WA hospital data and WA death registry data. Further clinical information about diagnostic tests performed and the principal reason for the patient’s admission to hospital or discharge from the ED will be abstracted from medical record reviews for a sample of patients.

The characteristics of the patients identified as potential candidates for non-transport to ED will be compared to those who were flagged as requiring transport to ED, with respect to:

a. Age, gender, socioeconomic status (based on residential address), geographical location, residential care facility, pre-hospital clinical problem code, ambulance dispatch priority code, time of day, day of week (SJA-WA data).

b. The Australasian Triage Score (ATS) [25] and presenting complaint recorded in ED.

c. ED diagnosis; ED disposition (discharge home; admit; died) and time in ED.

d. For those admitted to hospital: diagnosis, length of stay, procedures, disposition.

e. For all patients: representation at ED (or ambulance attendance) within 24 hours; 48 hours and within one week of the initial ambulance attendance.

f. A random sample of patients identified as being able to be managed in the community (proportionately across each hospital and major diagnosis category) will have medical record review by the study research nurse, to determine the nature of the clinical care received.

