#### Statistical analysis

a) The characteristics of each of the two groups (i.e. paramedic identified potential ECP candidate patients versus non-ECP patients) will be described using percentages for categorical variables; mean ± standard deviation and median with interquartile range for continuous variables.

b) Comparisons between the two groups (i.e. ECP candidate patients versus non-ECP patients) will be performed using chi-square tests for categorical variables; and Mann-Whitney ‘U’ (non-parametric) or t-test (parametric) for continuous variables, depending on the distribution of the data. Significance will be set at p<0.05.

c) Multivariable logistic regression models will be used to (i) estimate the odds of a patient being identified by the paramedics as an ECP candidate based on their demographic and clinical condition; and (ii) model the ED disposition (admit/not admit) based on the ECP candidate status identified by the paramedics, adjusted for potential confounding characteristics of the patient and/or condition. Covariates will be included on the basis of clinical plausibility and univariate associations. Models will be run with the inclusion of all covariates deemed relevant, i.e. not using any ‘step-wise procedure’. A-priori defined interaction terms will be tested and included in the models if significant.

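### Crude univariate association is an unsound entry criterion for the confounders in the admission model; fixing them in advance on clinical grounds costs nothing (minor)

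*Protocol article*

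**What the plan says.** Item c of the Statistical analysis section plans two multivariable logistic models. Model (i) is to "estimate the odds of a patient being identified by the paramedics as an ECP candidate based on their demographic and clinical condition". Model (ii) takes admit/not admit as outcome and candidate status as the exposure, "adjusted for potential confounding characteristics of the patient and/or condition".

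One rule governs covariates in both: "Covariates will be included on the basis of clinical plausibility and univariate associations". The next sentence begins "Models will be run with the inclusion of all covariates deemed relevant" and excludes step-wise selection. Interactions follow a separate rule: "A-priori defined interaction terms will be tested and included in the models if significant".

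The section gives no threshold for the univariate step. "Significance will be set at p<0.05" stands in item b, which covers the two-group comparisons. The section does not say whether a plausible covariate without a univariate association stays in, and it does not mention confidence intervals for these models.

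**The concern.** The plan rejects step-wise selection, yet lets the study data help decide which covariates enter. The sentence about entering everything relevant does not undo this, because relevance has just been defined partly by the univariate result.

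For model (ii) this conflicts with the model's purpose. Whether a variable confounds depends on its relation to admission and to candidacy given the other covariates, not on its crude relation to admission. Residential care is a possible example. Residents tend to be older, which raises admission. If they were admitted less often at a given age (an assumption; the article gives no data on it), the two effects could cancel in the crude comparison. The variable would then look irrelevant although it matters once age is in the model.

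At stake is the adjusted odds ratio for candidacy, in a study whose Background names patient safety as its main concern. Model (i) has no single exposure effect to confound. There the issue is only that p-values of predictors chosen on the same data are taken at face value.

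**Working it through.** **The plan's own figure.** The article states no sample size, power or precision for these models, so there is none to reproduce.

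**Cohort size.** The Background says that in 2012 crews "attended a total of 132,862 cases and 105,327 (79.3%) were transported to ED". Phase 1 states: "Over a 3 month period, we will include all patients within the Perth metropolitan area attended by SJA-WA paramedics". Assuming an even spread over the year, 105,327 / 4 = 26,332 transports per quarter.

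**Is there a need to screen?** The section on Perth EDs gives about 170,000 admissions from 580,000 attendances, or 29.3%. Applied to ambulance arrivals (assumption), 26,332 × 170,000 / 580,000 = 7,718 admissions. With 30 parameters (assumption), 7,718 / 30 = 257 per parameter. For model (i), if 5-10% are flagged (assumption), there are 1,317-2,633 flagged patients, or 44-88 per parameter. Neither model needs screening to be estimable.

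**How a masked confounder is lost.** Assumed inputs: true adjusted odds ratio for candidacy 0.30; one binary confounder present in 60% of flagged and 30% of unflagged patients; 50% admission among unflagged patients without it. Take a flagged share of 20% and a confounder odds ratio of 1.278.

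- Admission probabilities: flagged with the confounder 0.277, flagged without 0.231, unflagged with 0.561, unflagged without 0.500.
- Crude comparison on the confounder: with it, (0.12 × 0.277 + 0.24 × 0.561) / 0.36 = 0.466; without it, (0.08 × 0.231 + 0.56 × 0.500) / 0.64 = 0.466. The crude odds ratio is 1.00, so a 5% screen drops the variable in about 95% of samples by construction.
- Candidacy without the confounder: flagged 0.6 × 0.277 + 0.4 × 0.231 = 0.2586, odds 0.3488; unflagged 0.3 × 0.561 + 0.7 × 0.500 = 0.5183, odds 1.0760. The odds ratio is 0.3488 / 1.0760 = 0.324 instead of 0.30.
- Coverage: the bias on the log scale is ln(0.324/0.30) = 0.077. The standard error is √[1/(5,266 × 0.2586 × 0.7414) + 1/(21,066 × 0.5183 × 0.4817)] = 0.034. The bias is 2.25 standard errors, so a nominal 95% interval covers in about 38% of samples where the variable is dropped, or about 41% overall (0.955 × 0.385 + 0.045 × 0.95).

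**Simulation** of the same structure (n = 26,332; 1,000-1,500 samples per row; screen at p<0.05, an assumed cut-off):

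| Confounder | Flagged share | Dropped | Odds ratio after screening (true 0.30) | Coverage, screened | Coverage, fixed |
|---|---|---|---|---|---|
| Exactly masked (own OR 1.15) | 10% | 95% | 0.31 | 86% | 95% |
| Exactly masked (own OR 1.28) | 20% | 95% | 0.32 | 42% | 95% |
| Exactly masked (own OR 1.38) | 30% | 95% | 0.33 | 10% | 95% |
| Partly masked (crude OR 0.94 or 1.07) | 10% | 27-31% | 0.30 | 90-93% | 95% |
| Partly masked (crude OR 0.89 or 1.12) | 20% | at most 0.6% | 0.30 | 94-95% | 94-95% |
| Partly masked (crude OR 0.86 or 1.16) | 30% | 0% | 0.30 | 94-95% | 94-95% |
| Ordinary (own OR 1.1-1.5) | 20% | 0% | 0.30 | 94-96% | 94-96% |

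**Masking through age.** Two further sets made residential care the masked variable, with a true candidacy odds ratio of 0.40. All effect sizes are assumed, and the age effect is not restated here, so these are illustrations only.

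- Set 1 (120 samples; 10% flagged, 11% in care, conditional admission OR 0.46, crude OR 0.99): the variable failed the screen in 95% of samples. Leaving it out gave an odds ratio of 0.36 and coverage of 51%, against 96% with it in.
- Set 2 (100 samples per scenario; 12% flagged, 9% in care, conditional flagging OR 3, conditional admission OR 0.46-0.55): with a mean crude OR of 0.92-1.12, it failed in 33-95% of samples and coverage after screening was 72-93%. Omitting it gave 0.37-0.38. With a crude OR of 0.85, or 1.16 and above, it failed in at most 14% and coverage was 93-94%.

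The direction depends on the confounder: towards 1 in the table, away from 1 (flagged patients look safer) in the residential care sets.

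**The case against.** The strongest reply is that clinical plausibility is named first and everything relevant is then entered without step-wise deletion. If plausible variables stay in whatever their univariate result, screening loses none and the problem does not arise. That is correct, but the text does not say so, and a plain reading of the conjunction requires both criteria. On the looser reading, variables can enter on crude association alone; at 257 admissions per parameter a few extra covariates cost little.

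It can also be said that the covariate list belongs in a fuller protocol or SAP. The list may, but the selection rule is stated here. Residential care appears among the Phase 1 item a comparisons, so it may well be kept; it serves only as an example.

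A reader might infer several stronger claims that the article does not support:

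- Covariates are chosen by univariate association alone. Clinical plausibility is a co-criterion.
- A p<0.05 screen is planned. That level belongs to item b; its use above is an assumption.
- Both models are biased by lost confounders. Model (i) has no exposure effect to confound.
- Reported confidence intervals will be wrong. None is mentioned; the point concerns model-based inference if it is given.
- Coverage of 51%, or 10%, is to be expected. These come from near-exact or exact cancellation, and look severe because a cohort this large has narrow intervals.
- These are the only modelled results and decide the protocols. Phase 7 is systems modelling, and no adjusted odds ratio is named as what the clinical reference group decides on.

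**Conclusion.** The point holds as a minor one and a free improvement. Crude association in the study data is an unsound criterion for confounders in model (ii), and the wording allows a plausible confounder to be left out for lack of it. For model (i) the point extends only to pre-specifying predictors so that selection does not affect their p-values.

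The practical size is modest. With about 26,000 transports the effect is material only when masking is close to exact. In every scenario tried, flagged patients remained clearly less likely to be admitted. These results rest on assumed effect sizes, flagged shares and screening threshold, on an even spread of transports over the year, and on both criteria being required.

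**What to change.** Replace the covariate sentence in item c with wording such as: *The confounders for model (ii) are fixed before outcome data are examined, on clinical grounds, from the pre-hospital variables in Phase 1 item a, and all are kept whatever their univariate or adjusted p-value. The predictors for model (i) are likewise specified in advance. Univariate associations are reported for description only.*

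Item a already lists age, gender, socioeconomic status, location, residential care, problem code, dispatch priority and timing, all available from the ambulance episode. If the team also wants adjustment for the ED triage score or presenting complaint (item b), it can declare that as an additional model in advance. Levels of problem code and location should be grouped beforehand so that the parameter count stays near the 30 assumed above.

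The cost is one or two sentences, with no extra data and no change to the design.

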## Discussion

The results of our ‘virtual’ study of ECPs will provide much needed data to better inform decisions about emergency medical services in WA and other jurisdictions. Our study is congruent with the WA Department of Health primary health care principle of “implementation through consultation and evidence” [28]. Our project will bring together emergency physicians, ambulance service personnel and primary/community care providers (e.g. general practitioners and community nurses) to collaboratively develop alternative community based pathways of care for a group of patients who would otherwise be routinely (and possibly unnecessarily) transported to the ED. Collectively we will aim to develop a clinically appropriate and cost-effective alternative model of care for those patients who, despite calling for an ambulance, have health care needs that might be safely managed in the community. Reducing unnecessary ambulance transport to ED has the potential to reduce ED demand, ambulance ramping and ED crowding, as well as possibly reducing demand for in-patient services. However, we need evidence to establish that ECP models of care are safe, feasible and cost-effective.

## Abbreviations

EmCP: Emergency care practitioner; ECP: Extended care paramedic; SA: South Australia; NSW: New South Wales; WA: Western Australia; SJA-WA: St John Ambulance Western Australia.
